### Blinding

Blinding of subjects is not feasible given the nature of the intervention. While the intent is for the evaluation team to be blinded to intervention status, there are limitations to the extent that assessors can be blinded to participants’ intervention status, given that assessors live locally and intervention activities are visible in communities. However, team members are taking measures to support blinding where possible, including having separate intervention and evaluation field team members and holding separate team trainings and meetings.

### Data collection methods

#### Data collection team

All data collection will be conducted by trained assessors, most of whom have experience working in prior early childhood development trials. Assessors have at least a bachelor’s level education. Data collection will be overseen by the evaluation field lead and field research manager. All trainings will be conducted by the evaluation field lead and field research manager. Assessors will receive an initial 10-day training for all child and youth assessments, followed by a 1-day refresher training prior to round of data collection. To complete training, assessors must have > 95% agreement for all child and youth direct assessments with the evaluation field lead. Data collectors engaged in conducting qualitative data collection will receive an additional 1-week training in qualitative methods, followed by continued refreshers and debriefing sessions for each qualitative data collection activity. For the classroom observation tool, the field research manager and project coordinator will complete a training-of-trainers with an expert at the Universidad de los Andes, Bogota, Colombia. The field research manager will then train the evaluation field lead with support from the project coordinator. The field research manager and evaluation field lead will then deliver a 1-week training to a team of four assessors. Assessors will be required to achieve an interrater reliability of > 70% agreement with a Master Code in coding three 30–45-min videos in order to complete training. Coordination meetings will be held daily, with intensive debriefing meetings including capacity building activities held once per week. The evaluation field lead will conduct regular field visits to observe data collection to maintain quality. In each of the three steps, two assessments per assessor will be observed and independently scored for interrater reliability. Assessments will be video recorded and reviewed with team members during weekly debriefing meetings.

#### Data collection procedures for child and caregiver assessments

Assessors will conduct household visits to issue invitations to the study. If accepted, the assessor will enroll the caregiver in the study on site and administer the household questionnaire to the caregiver during the home visit. The assessor will evaluate the child at the household, and the child will be provided with a rest break and refreshments as needed. Questionnaires will be completed with caregivers using tablets. Data collection for the direct assessments will be conducted manually and then later entered in tablets. At the end of the session the child/caregiver will be given a thank you gift (e.g., book or toy).

#### Data collection procedures for youth participant assessments

CYLs will be issued an invitation to the study during the recruitment and training process. Assessors will issue invitations to comparison youth after completing the screening tool. The youth participant will either be enrolled and assessed on site or at a follow-up appointment, as is practical for the participant. The assessment will be conducted either at a recruitment workshop, training session, or during a home visit with the youth participant. All consecutive follow-up assessments will be conducted at the participant’s household, at the LEAPS school, or at an alternative community space identified for assessments. Location of assessments will be selected based on convenience for the youth participant and the availability of private space. All questionnaires will be collected using tablets. Executive functioning assessments will be conducted manually and later entered in tablets. Youth participants will receive a thank you gift (e.g., a LEAPS mug) and refreshments for participation.

#### Data collection procedures for classroom observations

Assessors will first obtain permission from the local government and school leadership for the observations, after which they will visit schools to coordinate with the teacher and supervisor to schedule the observation. Assessors will arrive before the start of the school day when possible. Assessors should ensure that they are able to observe a minimum of 2.5 h of the classroom session. If there is less than 2.5 h of the session remaining, the observation should be rescheduled. If a teacher/CYL is absent, the observation will be rescheduled. Assessors should conduct a maximum of two visits: if the teacher/CYL is absent on the first visit, the assessor will reschedule and conduct a second visit. If the teacher/CYL is absent on the second visit, then the school will no longer be included in the data collection round. The observation may be video recorded as an additional resource to reference when determining final scores. Assessors will observe the class without interrupting the school routine or activities. Assessors will take notes throughout the session and manually complete the observation tool after the session. Videos may be reviewed for items where there is a discrepancy in scoring.

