## Objectives

The present study has five objectives:
Objective 1: To evaluate the impact of the larger-scale implementation of the LEAPS model on children’s school readiness and executive functioning;Objective 2: To evaluate the impact of the larger-scale implementation of the LEAPS model on female youth development;Objective 3: To evaluate the larger-scale implementation of the LEAPS model as integrated in NCHD platforms and delivered through NCHD systems in order to assess fidelity, demand, enablers, and barriers to implementation and quality;Objective 4: To evaluate the readiness of NCHD to uptake LEAPS for sustainable scaling and replication in other districts and provinces in Pakistan, with respect to leadership and governance, training, supervision, advocacy and communication, monitoring and evaluation, and financing and resource mobilization; andObjective 5: To examine cost-per-beneficiary ratios through a cost evaluation.

It is hypothesized that after implementation of LEAPS, clusters will experience significantly improved population-level outcomes for school readiness among children aged 4.5-5.5 years as assessed by the IDELA, as well as improvements in children’s executive functioning skills. We also hypothesize that female youth who participate in LEAPS will have improved outcomes for executive functioning, and personal and professional development relative to youth who are not LEAPS participants.

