#### Classroom observations

To examine quality of the preschool environment, classroom observations will be conducted in both LEAPS classrooms and comparison preschool classrooms. As LEAPS schools are by design typically the only preschool service operating in an intervention cluster, in order to select the most suitable comparison, the comparison preschool classrooms will be selected based on the following: (i) location: school should be located as close to the LEAPS evaluation cluster as possible; and (ii) prioritizing enrollment of government schools (standard service) where available, followed by NCHD-operated schools and other options (private/Madrasa) to reflect the distribution of these types of schools in rural communities in the targeted districts. Comparison classrooms may vary with respect to the preschool classroom arrangements, including grade-level groupings (stand-alone preschool classrooms or multi-grade classrooms), single- or mixed-gender classroom, and informal or formal settings. One comparison classroom teacher will be enrolled for each LEAPS school. All Step 1 and Step 2 LEAPS schools (*n* = 66) and equivalent number of comparison schools will be observed at two timepoints: once in Step 2 (mos. 14–16) and once during Step 3 (mos. 21–24). All Step 3 LEAPS schools (*n* = 33) and equivalent number of comparison schools will be observed at one timepoint in Step 3 (mos. 21–24).
Eligibility criteria:
◦ LEAPS school: Must be located in an intervention cluster.◦ Comparison preschools: Fits criteria for location, type of school, and gender make-up.Exclusion criteria: None

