***Mediator***		
Classroom Structural and Process Quality	To be adapted from the Measure of Early Learning Environments (MELE) module of the Measuring Early Learning Quality and Outcomes (MELQO) tool [54] and the Instrument for Measuring Quality of Early Childhood Education in Colombia (IMCEIC) [55]	Direct Assessment of children’s pre-primary learning environments in LEAPS preschool and comparison classrooms. The 7 major domains are: environment and physical setting, family and community engagement, personnel, interactions, inclusiveness, pedagogy, and play. Mean scores will be calculated from all items (range 1–4 points). Higher scores reflect better outcomes.

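### A school whose teacher or CYL is absent at two visits leaves the classroom-observation round, so the quality score describes only schools with a teacher present and may under-represent poorly functioning centres

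*Protocol article*

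**What the plan says.** All places are in the protocol article. Under Classroom observations, "classroom observations will be conducted in both LEAPS classrooms and comparison preschool classrooms". The Abstract promises an assessment in each LEAPS centre. The Classroom observations section refers to all LEAPS schools: for the 66 Step 1 and Step 2 schools, these "and equivalent number of comparison schools will be observed at two timepoints: once in Step 2 (mos. 14–16) and once during Step 3" (months 21–24); for the 33 Step 3 schools, these "and equivalent number of comparison schools will be observed at one timepoint in Step 3 (mos. 21–24").

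The section on data collection procedures for classroom observations makes that coverage conditional. Visits are arranged beforehand: after permission is obtained, "they will visit schools to coordinate with the teacher and supervisor to schedule the observation". Then "Assessors should conduct a maximum of two visits", and "If the teacher/CYL is absent on the second visit, then the school will no longer be included in the data collection round". The rule makes no distinction between LEAPS and comparison schools.

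Table 3 lists classroom structural and process quality as the only mediator: "Mean scores will be calculated from all items (range 1–4 points"). The Impact evaluation section uses these data as a predictor in adjusted analyses. Objective 3 is to evaluate larger-scale implementation "in order to assess fidelity, demand, enablers, and barriers to implementation and quality".

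**The concern.** Whether a school has a score depends on whether its teacher kept one of two arranged appointments. That is close to what the instrument is meant to measure. If schools with absent teachers tend to be weaker, the mean quality of the observed schools is higher than that of the schools the trial set out to describe.

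The observation tool is the only quality measure in the article applied to both LEAPS and comparison schools. It is also scored by evaluation assessors rather than by the implementing partner's own supervisors. A loss that depends on quality therefore cannot be fully made good from other sources. The Implementation evaluation section itself gives as a purpose the avoidance of judging an intervention that was not adequately delivered. A centre whose teacher is repeatedly absent may be such a case, and the rule as written assigns it no result in this instrument.

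**Working it through.** The article states no absence rate and no power or precision figure for the classroom observations, so there is no figure of its own to reproduce. What follows is illustration under stated assumptions.

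**Inputs from the article.** At most two visits per school per round; 66 LEAPS schools in the Step 2 round; 66 + 33 = 99 LEAPS schools in the Step 3 round, of which 33 have only that round; an equal number of comparison schools; score range 1–4.

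**Assumed.** Absence probability per visit *a* = 5–30%. Dropped schools would score *d* = 0.5–1.0 points lower than observed schools.

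**Step 1: schools lost.** If the two visits are independent, the share dropped in a round is *q* = *a*². The expected number of Step 1/2 schools missing both rounds is 66 × *q*².

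| *a* | *q* = *a*² | of 99 LEAPS (Step 3 round) | of 33 Step 3 schools (no score at all) | of 66 Step 1/2 schools, both rounds |
|---|---|---|---|---|
| 5% | 0.25% | 0.25 | 0.08 | 0.0004 |
| 10% | 1% | 0.99 | 0.33 | 0.007 |
| 20% | 4% | 3.96 | 1.32 | 0.11 |
| 30% | 9% | 8.91 | 2.97 | 0.53 |

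If absence clusters in the same schools, more are lost. In the limit where a fixed set of schools is always absent, *q* = *a*: at 20%, 0.20 × 99 = 19.8 LEAPS schools.

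**Step 2: shift in the mean.** The mean over all schools is (1 − *q*) × observed mean + *q* × mean of dropped schools. Hence observed mean − full mean = *q* × *d*.

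| *q* | *d* = 0.5 | *d* = 1.0 |
|---|---|---|
| 1% | 0.005 | 0.01 |
| 4% | 0.02 | 0.04 |
| 9% | 0.045 | 0.09 |
| 15% | 0.075 | 0.15 |

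**Step 3: extreme case.** With an observed mean of 3.0 and every dropped school at the floor of 1, *d* = 2. Then 5% dropped gives 0.05 × 2 = 0.10, and 20% dropped gives 0.20 × 2 = 0.40. Under independent visits, 5–20% dropped needs √0.05 = 22% to √0.20 = 45% absence per visit, or else chronic absence in that share of schools.

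**Step 4: the contrast.** The bias in the LEAPS-minus-comparison difference is *q*(LEAPS) × *d*(LEAPS) − *q*(comparison) × *d*(comparison). With *d* = 1 in both groups, 1% dropped in LEAPS and 9% in comparison gives 0.01 − 0.09 = −0.08; the reverse gives +0.08. The sign is not determined by anything in the article.

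**The case against.** The strongest objection is that the rule is ordinary fieldwork. Interactions and pedagogy cannot be scored without a teacher, revisits have to be capped, and a score cannot be invented. That stands: the visit limit is not an error. The point concerns what becomes of the school afterwards.

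A reader might infer that the worst centres vanish from the trial's quality and fidelity results, so that non-operation goes undetected. The documents do not support this, for four reasons.

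- Fidelity has other sources. Field officers complete a quality and fidelity checklist at monthly visits (Supervision visits). Administrative and programmatic data, interviews and focus groups feed the implementation evaluation and its trend analyses. None is subject to the two-visit rule.
- Exclusion applies to one round, so Step 1 and Step 2 schools can still be scored in the other.
- The article gives no absence rate and no link between absence and quality. Two absences can be illness or travel.
- The article does not say that absences go unrecorded. Handling of missing scores may stand in the full protocol (Additional file 2) or an analysis plan, neither of which was available here.

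Two further points limit the consequence. The primary IDELA analysis uses the population survey and does not depend on these scores. The sentence on quality as a predictor follows the school-cohort sentences; if it refers to that cohort, the schools concerned are the 33 Step 1 schools, which have two rounds, and an upward shift in mean quality does not by itself bias a slope. What could still be lost there is range in the predictor, and up to 10 of the 330 children for each Step 1 school without a score.

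The objection does not remove the stated rule, which takes a school out of the round for a reason plausibly related to the quantity measured. An analysis plan can repair that only if the absence is kept as data.

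**Conclusion.** The point holds in a limited form. The rule makes the classroom-quality score conditional on teacher presence, in tension with the stated intention to observe every LEAPS school. Poorly functioning centres may be under-represented, and a Step 3 school that meets the rule has no score at all.

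The likely size is small unless absence is common or chronic: 0.005–0.09 points if 1–9% of schools are dropped and would score 0.5–1.0 lower. The 0.40 figure is a near-extreme bound and should not be read as an expectation. All these sizes rest on assumed absence rates and score differences. An upward shift in a group mean also assumes that absent schools are weaker. The bias in the LEAPS–comparison contrast could go either way. This is a cheap improvement to a secondary instrument and does not threaten the trial's main result.

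**What to change.** Replace removal from the round by a recorded outcome. The school stays in the denominator with the result 'teacher/CYL absent at two visits' and no quality score. Beside each mean score, report the number of such schools by LEAPS or comparison, by step and by round. Repeat the quality contrast and the predictor analysis with low values assigned to these schools, down to the scale minimum of 1, and label the result as a bound rather than a measured score. The label matters because the tool also covers domains such as physical setting, for which a teacher's absence is not evidence of minimum quality.

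The change needs no extra visit. It costs one code on the form and one additional analysis, and reported quality may look slightly less favourable. If rounds are already complete, the counts can probably be recovered from the logs of data collection activities mentioned under Reporting and risk of adverse events and harms. Individual absences should not be passed to the NCHD district offices as part of this change, because the Blinding section keeps the delivery and evaluation field staff apart.

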#### Qualitative data collection procedures

All IDIs and FGDs will be conducted by data collectors trained in interview techniques. All activities will be conducted to ensure the participant’s privacy and comfort, and to minimize risk of disturbances. The IDIs and FGDs will be semi-structured, using pre-piloted topic guides and will be recorded. The FGDs will additionally be observed by a data collector trained as a note-taker.

### Data management

Data is collected on encrypted tablets and will be uploaded from the tablets to an encrypted server maintained by the Aga Khan University Data Management Unit (DMU). Paper-based assessments (i.e., classroom observation tool) will be entered in the DMU database using FoxPro by the DMU research assistant at the field office. Initial checks for quality assurance will be conducted by the DMU research assistant and a DMU data coordinator in collaboration with the evaluation field lead. Data will be shared via regular secure transfers with the team members at Harvard, where it will be uploaded to a password-protected shared Dropbox folder. Access to the data folder will only be given to the research team. At Harvard, the database will be managed by the data analyst and project coordinator, with regular cleaning and checks for quality assurance. All data will be de-identified and the keys linking identifiers to participants will be stored in a password-protected folder. Data will be wiped from the tablets after the round of data collection activities have been completed. All video and audio recordings will be securely stored on a password-protected computer at the field office managed by the evaluation field lead and will be deleted from the camera/recorder after uploading. Recordings will be deleted after analysis is complete (i.e., within 1 year of endline). Paper-based data assessments will be stored in a locked cabinet at the field site.

Qualitative data will be transcribed in Sindhi by assessors. Five percent of recordings will be randomly chosen by the field research manager and evaluation field lead to check quality of transcription. Transcripts will be translated from Sindhi to English by a translator outside of the project team. Five percent of translations will be chosen randomly for independent back translations. Transcripts, notes, and photos from original qualitative data collection activities will be managed through a password-protected shared Dropbox folder. Only research team members will have access. All data will be de-identified and the keys linking identifiers to participants will be stored in a password-protected folder. Audio recordings will be securely stored on a password-protected computer at the field office managed by the evaluation field lead and will be destroyed after the project has been completed.

### Analysis

#### Impact evaluation

The primary analysis will use the intent-to-treat principle. Baseline balance will be tested between randomized groups to see whether randomization was successful. The primary outcome, IDELA total score, will be computed for each individual using the parameter estimates from the Graded Response Model, as recommended by the tool developers. We will assess the effect of the LEAPS intervention using the analytical framework proposed by Hussey and Hughes [71] for analysis of stepped wedge cluster-randomized trials. Estimation of treatment effects will be obtained from a generalized linear mixed model (GLMM) to produce the mean difference in IDELA scores for LEAPS intervention versus control. The GLMM will include a fixed effect for stratified randomization group, a random effect for cluster, a fixed effect for time, and use an exchangeable correlation structure. In addition, the study will perform a set of sensitivity analyses to explore potential deviations from the basic SW-CRT model proposed by Hussy and Hughes [71]. The closed school cohort data will be to examine the changes in the average school readiness among children participating in the LEAPS preschool between baseline and endline. Longitudinal data collected for school cohort participants will be linked using participant IDs. The preschool classroom structural and process quality data and the child household characteristics will serve as predictors of interest in adjusted analyses. Youth cohort data will be analyzed to examine differences in outcomes over time among CYLs as compared to the youth comparison group. Longitudinal youth participant data will be linked using participant IDs. Analysis will account for CYLs’ length of program exposure and adjust for potential confounding variables, including age, education, marriage status, assets-based household socio-economic status, and household food insecurity. No interim analyses are planned.

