#### Population survey

A cross-sectional survey of child-caregiver dyads will be conducted at four timepoints: at baseline (Step 0; mos. 1–3) and again at the end of each consecutive step, with 7 months between data collection rounds. Eleven children aged 4.5–5.5 years and their caregivers will be enrolled in the population survey from each of the 99 clusters (1089 child-caregiver dyads total), regardless of the child’s enrollment in the LEAPS preschool program. The primary objective of the population survey will be to assess changes in the average school-readiness over time. With this trial design, rather than assessing program impact on specific individuals, we are aiming to assess the impact of LEAPS on local (cluster-level) school readiness, which is a function of both the proportion attending LEAPS and the impact on the treated. By including both LEAPS participants and children who are not participating in the LEAPS program, this design will allow us to separate treatment effects on the treated from average (intent-to-treat) effects at the population level. The sample will be drawn from village birth registries provided by NCHD, which will be verified (a) by cross-checking against birth registries from local community health workers; and (b) through household visits conducted by research team members. The sample will be re-drawn at each of the four data collection timepoints. Children may be enrolled for assessment at multiple timepoints. Assessors will use a random number generator to select 11 participants/cluster using the verified lists of eligible children prepared for each cluster. If a participant refuses, assessors will select the next participant in the random sequence.
Eligibility criteria: Child is age 4.5–5.5 years ± 2 weeks (i.e., 53.5–66.5 months at the time of the survey) and resides in the targeted villageExclusion criteria: Child or caregiver shows signs of severe clinical health condition or disability

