***Covariates***		
Child's Household Demographics	Child Household Questionnaire, including Socio-Economic Status Index [68]*; Household Food Insecurity Access Scale (HFIAS) [69]*	Household questionnaire including items examining child’s age, child’s gender, parental education, parental employment, assets-based household socio-economic status, and household food insecurity.
Child Anthropometric Indices	Anthropometric Questionnaire*	Anthropometric Questionnaire collects child age and child growth indicators. Child’s anthropometric *z* scores will be calculated using WHO Child Growth Standards.
Youth’s Household Demographics	Youth Enrollment Questionnaire, including Socio-Economic Status Index [68]*; Household Food Insecurity Access Scale (HFIAS) [69]*	Youth Enrollment Questionnaire including items examining the youth’s demographics, such as age, education, marriage status, assets-based household socio-economic status, and household food insecurity.

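### The primary model as listed does not include child age, a covariate already collected; prespecifying it is a small, free gain in precision

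*Protocol article*

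**What the plan says.** Under Analysis, Impact evaluation, the primary model is specified in one sentence: "The GLMM will include a fixed effect for stratified randomization group, a random effect for cluster, a fixed effect for time". The rest of that sentence says only that the correlation is taken as exchangeable. No child-level covariate is named.

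Under Population survey, the eligibility rule is "Child is age 4.5–5.5 years ± 2 weeks (i.e., 53.5–66.5 months at the time of the survey"), which is a span of 13 months.

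Table 3 places age and sex under Covariates: "Household questionnaire including items examining child’s age, child’s gender, parental education, parental employment". A second covariate row also records age: "Anthropometric Questionnaire collects child age and child growth indicators". Table 3 describes the IDELA total as a Graded Response Model score and says outcomes are recorded as absolute values. It describes no age standardisation.

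Two other sentences in the Impact evaluation section bear on the point:
- Adjusted analyses are mentioned: "the child household characteristics will serve as predictors of interest in adjusted analyses". This comes directly after the school-cohort text and is not tied to the population-survey model.
- Sensitivity analyses are planned: "the study will perform a set of sensitivity analyses to explore potential deviations from the basic SW-CRT model". Their content is not given.

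The youth analysis in the same section does name its adjustment variables, and age is among them.

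**The concern.** A score from a direct assessment of early learning would be expected to rise with age in months. If it does, part of the child-to-child variation within a cluster-round is age. A model without age leaves that part in the residual. The fixed effects for time remove only age shifts that all clusters share in a given round.

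What is at stake is the width of the confidence interval for the primary effect and the clarity of the prespecification. Table 3 calls age a covariate, but the article does not say which population-survey model uses it.

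**Working it through.** **Inputs from the protocol article**
- 99 clusters, 33 crossing over at each of 3 steps, and 4 survey rounds (Study design; Population survey).
- 11 children per cluster per round, ICC 0.175, target effect 0.3 SD (Sample size and power calculation).
- Age window 53.5 to 66.5 months, which is 13 months (Population survey).

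**Assumptions, not in the documents**
- Ages are uniform over the window and independent within cells.
- IDELA rises linearly by b = 0.025 to 0.10 SD per month (0.3 to 1.2 SD per year).
- Total variance is 1, and alpha is 0.05 two-sided.

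**Step 1. Standard error without age.** The Hussey-Hughes variance, with I = 99 and T = 4, is

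Var = I·s²(s² + T·t²) / [(I·U − W)s² + (U² + I·T·U − T·W − I·V)t²]

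- U = 33 × (3 + 2 + 1) = 198
- W = 33² + 66² + 99² = 15246
- V = 33 × (9 + 4 + 1) = 462
- Coefficient of s²: 99 × 198 − 15246 = 4356
- Coefficient of t²: 39204 + 78408 − 60984 − 45738 = 10890
- t² = 0.175 and s² = 0.825/11 = 0.075

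Var = 99 × 0.075 × 0.775 / (326.7 + 1905.75) = 5.754 / 2232.45 = 0.002578, so SE = 0.0508.

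**Step 2. The plan's own power figures.** The article states 80% power with 8 children per cluster and 90% with 11. With the inputs above, this model gives 99.9% with 8 (SE 0.0590) and more than 99.9% with 11 (0.3/0.0508 = 5.9 standard errors). The stated figures are therefore not reproduced. That is a separate matter and does not bear on age adjustment.

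**Step 3. Standard error with age.** The age variance is 13²/12 = 14.08, an SD of 3.75 months. Adjusting removes b² × 14.08 from the within-cell variance of 0.825.

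| b (SD/month) | variance removed | share of 0.825 | SE with age | fall in SE | variance ratio |
|---|---|---|---|---|---|
| 0.025 | 0.0088 | 1% | 0.0505 | 0.5% | 1.01 |
| 0.042 | 0.0245 | 3% | 0.0500 | 1.4% | 1.03 |
| 0.05 | 0.0352 | 4% | 0.0497 | 2.1% | 1.04 |
| 0.08 | 0.0901 | 11% | 0.0480 | 5.4% | 1.12 |
| 0.10 | 0.1408 | 17% | 0.0464 | 8.5% | 1.20 |

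The variance ratio reads approximately as the equivalent increase in children per cell: about 1% to 20%.

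The table assumes one constant cluster effect, as the article's exchangeable structure does. If the cluster effect is less stable over time, the gain is smaller. With a cluster autocorrelation of 0.8, the fall runs from 0.3% to 5.6% over the same slopes. With 0.5, it runs from 0.2% to 3.6%.

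**Step 4. Chance age imbalance.** The mean age of a single cell of 11 children has an SD of 3.75/√11 = 1.13 months. The treatment effect, however, is a contrast over 99 × 4 = 396 cells. Applying the same generalised least squares weights to independent ages gives a contrast with an SD of about 0.20 months. Multiplied by b, it moves the estimate by 0.005 SD (b = 0.025) to 0.020 SD (b = 0.10).

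This movement is the same quantity as the lost precision. At b = 0.10 the variance falls from 0.002578 to 0.002156, and √0.000422 = 0.0205, which matches 0.10 × 0.2045 = 0.0205. The unadjusted standard error already contains it.

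**Step 5. Effect on the stated power.** If the article's 80% and 90% are taken at face value and the SE is scaled by Step 3, power becomes Φ((1.96 + z)/ratio − 1.96), where z is the normal quantile of the stated power. The 80% becomes 80.4% (b = 0.025) to 86.5% (b = 0.10), and the 90% becomes 90.3% to 94.3%.

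**The case against.** The strongest objection is that this is an omission in a condensed article. The list of model terms is plainly not exhaustive, since it does not name the intervention term either. The full protocol and any SAP are not shown and may list covariates. Table 3 points towards using age, and adjusted analyses are mentioned. The unadjusted Hussey-Hughes model is a recognised and valid primary analysis.

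Most of this stands, and it keeps the point minor. What remains is that the article labels age a covariate and names age for the youth analysis, but ties no child covariate to the population-survey model. The one sentence on adjusted analyses follows the school-cohort text, so its reach is unclear.

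Two stronger readings are tempting, and the documents support neither.
- A reader might infer that age imbalance biases the effect. Clusters are randomized, children are drawn at random within clusters and redrawn each round, and time is a fixed effect. Chance age differences are therefore random error, already counted in the standard error. The 1.13 months for one cell is not the relevant scale; the 0.20 months for the contrast is.
- A reader might infer that power is at risk. Step 2 gives more than 99% power without age, and adjustment can only add to the powers that the article states.

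The size also depends on a slope that the documents do not give. At the weak end (0.025 to 0.042 SD per month) the standard error falls by only 0.5% to 1.4%.

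**Conclusion.** The point holds as a minor one about precision and prespecification. The primary model as listed is valid and unbiased, but it does not use a covariate that the trial collects and that probably predicts the outcome. The cost is a standard error about 0.5% to 9% larger than it need be, worth about 1% to 20% more children. This rests on an assumed slope of 0.025 to 0.10 SD per month, uniform and independent ages within the window, and a constant cluster effect. A less stable cluster effect makes the gain smaller; age clustering within cluster-rounds would enlarge the chance contrast. No gain was calculated for sex, or for outcomes other than the IDELA total.

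**What to change.** State in the Impact evaluation section that the primary population-survey model includes child age in months (linear, with a quadratic term if prespecified) and sex as fixed effects, beside the intervention, stratum, time and cluster terms. State the same for the secondary child-outcome models (IDELA domains and executive function). Report the unadjusted model as supportive. If the full protocol or SAP already specifies this, a cross-reference is enough.

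The cost is a sentence of model wording, settled before the outcome data are analysed. Both variables are already collected for surveyed children, and neither can be changed by the intervention.
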